##### Web-based exercise prescription

Participants are individually prescribed an 8-week multi-modal (resistance, aerobic and flexibility) programme based upon the conservative prescription used in Galvão et al. (Table 2) and isometric spinal exercise prescription applied in Rief et al. [14, 15]. Exercise prescription variables can be autoregulated by re-completing module assessment questions using the links on the homepage. The intensity or volume of session regulated can be modified by participants modifying their fatigue ratings, pain levels and confidence. Resistance exercises which produce pain can also be changed by adjusting the movement-based questions (e.g. Do you experience pain when you bend or straighten your elbow whilst holding a heavy item?). Participants are educated on autoregulation via the safety and exercise plan modules and programme modification through computer-tailoring is discussed in the initial tele-coaching session).

**Table 2 Tab2:** Modified multimodal exercise prescription for individuals with bone metastases [14]

Metastasis Location	Resistance			Aerobic		Flexibility
	Upper	Trunk	Lower	WB	NWB	
Proximal humerus		^✓^	^✓^	^✓^	^✓^	^✓d^
Cervical spine	^✓a^		^✓^	^✓^	^✓^	^✓c^
Thoracic spine/ribs	^✓a^		^✓^	^✓^	^✓^	^✓c^
Lumbar spine	^✓^		^✓^		^✓^	^✓c^
Pelvis	^✓^	^✓^	^✓b^		^✓^	^✓c^
Proximal femur	^✓^	^✓^			^✓^	^✓e^

*WB* weight bearing (walking); *NWB* non-weight bearing (water walking; cycling)

^✓^Target exercise region

^a^Exclusion of shoulder flexion/extension/abduction/adduction—inclusion of elbow flexion/extension

^b^Exclusion of hip extension/flexion—inclusion of knee extension/flexion

^c^Exclusion of spinal flexion/extension/rotation

^d^Exclusion of elbow flexion/extension

^e^Exclusion of knee flexion/extension

##### Resistance-based component

There are twenty-seven possible resistance exercises available for prescription (Supplementary Table 2), which have been used in Galvão et al. and Rief et al. [14, 15]. However, dependent on the algorithm, participants will be prescribed between three and eight exercises. Unpublished usability testing on eleven men reported a median of six exercises prescribed per person. Each resistance exercise will be accompanied by a video demonstration (see Fig. 4) and written exercise instructions to aid both safety and efficacy. Participants will be mailed four resistance exercise bands of different loads, which match the resistance bands used within the videos as well as a door anchor to help them to complete the exercises prescribed. Moreover, participants with access to home-based or gym resistance training equipment (e.g. dumbbells) will be encouraged to replicate the exercises with their equipment if possible. Eccentric and concentric phases are performed over a period of 2 seconds each to reduce peak forces transmitted to the skeleton [12–14].

**Fig. 4 Fig4:**
[figure not shown]
Example of the video demonstrations provided in Exercise Guide website, (**a**) standing band row and (**b**) squat

Intensity will be prescribed individually using the OMNI resistance exercise scale of perceived exertion (Fig. 5) and will range between seven to eight out of ten (moderate-vigorous intensity) as determined by current fatigue levels and both resistance training experience and confidence [50]. This variability has been built in to help balance adherence with the stimulus needed to see clinically relevant outcomes. A 12- to 8-repetition maximum has been prescribed for two to three sets per exercise (Table 3). Self-reported questions at the end of week three will allow researchers to monitor compliance. Participants unable to comply to at least 80% of the prescription (based on total sessions completed and compliance to volume prescribed) will be given a modified prescription for the last five weeks (Supplementary Table 3) to ensure the participant does not increase repetitions or sets too rapidly. To encourage progression, participants will be instructed to increase the resistance of the upper and lower body exercises by self-assessed 5-10% if the rate of perceived exertion standards were exceeded in each exercise set completed [14].

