The use of technology in distance-based health care, otherwise known as eHealth, may help to improve the capacity of distance-based programmes. For example, web-based platforms have the ability to prescribe and demonstrate tailored exercise plans, provide tailored behavioural change advice, facilitate self-monitoring and support communication with healthcare professionals. Much of this can be achieved in an automated fashion using computer-tailoring techniques, thus allowing for personalization at a low-cost [26]. Reviews of digital health interventions for behaviour change suggest that some level of human support is important for efficacy [27, 28]. E-Health interventions utilising some of these techniques to support prostate, colorectal, breast and leukaemia cancer populations have already been trialled with good effects in terms of improved physical activity levels and reduced sedentary behaviour [24, 29–32]. However, the extent to which these techniques are acceptable, safe and potentially effective for supporting individuals with metastatic prostate cancer, given their unique needs and risk profile, is unknown. Our study seeks to address this gap by conducting a pilot evaluation of ExerciseGuide, a web-based and telephone supported personalised exercise intervention designed for individuals living with metastatic prostate cancer.

The primary objective of the trial is to assess key areas of uncertainty regarding the use of ExerciseGuide (and other similar programmes) in future practice and research, including issues relating to feasibility, safety and potential for efficacy. Publication of this protocol aims to ensure transparency around pre-specified criteria for success, aid replication of study and intervention methods and inform interested parties of the upcoming trial results.

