##### Aerobic-based component

Individuals with bone metastases will be prescribed either stationary cycling, water walking or walking. For individuals without bone metastases, other modes such as conventional cycling, rowing or cross trainers are also prescribed. Equipment accessibility, metastasis location, pain and preference influence what mode is prescribed. For individuals currently completing two sessions or less a week, two sessions a week will be prescribed for the first 3 weeks. If individuals are completing three or more sessions, then they will be prescribed three specific aerobic sessions. Individuals are encouraged to complete extra aerobic sessions if they feel capable. In terms of duration of sessions, participants will complete 2-3 sets of between 6 and 15 min, with rest intervals ranging from 0 to 5 min or 1 session of 30 min with no prescribed rest (Table 4). Session duration and rest intervals will be based on what activity duration the participant feels is feasible, if they are currently meeting this level and an ability score based on previous experience, levels of fatigue and confidence for completing two sessions per week. Intensity will be prescribed using the OMNI aerobic exercise scale of perceived exertion [50]. Intensity will be prescribed individually and will be between six and seven out of ten (moderate intensity) as determined by current fatigue levels and both experience and confidence.

**Table 4 Tab4:** Aerobic training prescription for session duration based on participant self-assessment of exercise duration feasibility, current participation and ability

Duration feasible	Meeting duration	Ability	Aerobic prescription	Total active minutes
0-4 min	No	Low/High^a^-	2 × 3-min efforts with 3-5 min rest	6 min
0-4 min	Yes	Low/High^a^	2 × 4-minute efforts with 3-5 min rest	8 min
5-9 min	No/yes^a^	Low	2 × 5 minutes with 2 min rest	10 min
5-9 min	No/yes^a^	High	3 × 5 minutes with 2 min rest	15 min
10-19 min 10-19 min	No/yes^a^ No	Low High	2 × 10-min efforts with 5-min rest	20 min
10-19 min 20-29 min	Yes No/yes^a^	High Low	2 × 15-min efforts with 5-min rest	30 min
20-29 min 30-44 min 30-44 min 45-59 min 60 min +	No/yes^a^ No Yes No/yes^a^ No/yes^a^	High High Low Low Low	1 × 30-min effort	30 min
30-44 min 45-59 min 45-59 min 60 min +	Yes No Yes No/yes^a^	High High Low High	3 × 10-min high intensity	30 min
Unknown	No/Yes^a^	High/low^a^	2-3 × 5-10 min efforts with 2-5 min rest	10-30 min

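### As printed, the resistance-progression rule runs backwards: participants add 5-10% load when every set felt harder than prescribed

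*Protocol article*

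**What the plan says.** The Resistance-based component section sets each participant's effort on the OMNI resistance scale, which "will range between seven to eight out of ten (moderate-vigorous intensity"). The level depends on fatigue, training experience and confidence. For volume, "A 12- to 8-repetition maximum has been prescribed for two to three sets per exercise".

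The section closes with the load rule: "To encourage progression, participants will be instructed to increase the resistance of the upper and lower body exercises" by a self-assessed 5-10% "if the rate of perceived exertion standards were exceeded in each exercise set completed".

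The Aerobic-based component section uses the aerobic version of the scale, where intensity "will be between six and seven out of ten (moderate intensity").

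The Introduction gives one reason for publishing the protocol, which is to "aid replication of study and intervention methods and inform interested parties".

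**The concern.** A progression rule tied to perceived exertion should hold effort near its target: add load when the work feels too easy, and hold or reduce it when the work feels too hard. The printed sentence does the opposite. A participant who rates every set above the prescribed level is told to add load, which pushes the next session further above target. A participant who finds every set too easy gets no instruction to progress.

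Two things are at stake.

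- **Replication.** Anyone rebuilding the programme from the article would copy a reversed trigger.
- **Participant instruction.** The sentence describes something participants apply themselves, at home. The programme otherwise limits skeletal loading, through the site restrictions in Table 2 and the slow lifting tempo. If the website, the exercise instructions or the coaching script was written from the same sentence, participants would receive it too. That cannot be seen from the article and needs checking.

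**Working it through.** The plan gives no figure to reproduce, and no sample size or power formula applies. The check is of direction.

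**Step 1: what is exceeded.** The sentence names perceived exertion standards. The only such standard stated for resistance work is the OMNI level of 7 to 8 out of 10.

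**Step 2: which way the scale runs.** The article labels 6-7 moderate for aerobic work and 7-8 moderate-vigorous for resistance work. Both labels fit a scale on which a higher score means harder effort. Exceeding the standard therefore means effort harder than prescribed.

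**Step 3: which ratings trigger an increase.** The article says only that the scale is out of ten, so whole-number ratings from 0 to 10 are assumed. Let r be the rating given in every set. Three rules are compared:

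- Printed rule: add load if r is above the standard.
- Alternative A (exertion below target): add load if r is below the standard.
- Alternative B (repetitions exceeded at or below target exertion): an increase is possible only if r is at or below the standard.

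| Standard | Printed rule | Alternative A | Alternative B can apply | Ratings shared with printed rule |
|---|---|---|---|---|
| 7 | 8-10 (3 values) | 0-6 (7 values) | 0-7 (8 values) | 0 with A, 0 with B |
| 8 | 9-10 (2 values) | 0-7 (8 values) | 0-8 (9 values) | 0 with A, 0 with B |
| 7-8 as a band | 9-10 (2 values) | 0-6 (7 values) | 0-8 (9 values) | 0 with A, 0 with B |

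The lack of overlap follows from the definitions and is not an empirical result. It shows that the printed rule is not a looser form of either sensible rule.

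**Step 4: reach of the rule.** It covers 2 of the 3 exercise types in Table 3 (upper and lower body, not trunk). It must be met in all 2 or 3 sets, and each trigger adds 5-10%.

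**Step 5: whether another part of the article corrects it.**

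- Web-based exercise prescription describes a separate route, in which participants re-answer questions on fatigue, pain and confidence. It says that "programme modification through computer-tailoring is discussed in the initial tele-coaching session", but does not restate the load rule.
- The week-three check in the resistance section changes the prescription for those below 80% compliance, so that repetitions or sets do not rise too fast. It does not set the direction of the load rule.
- Table 3 gives sets and repetitions only.
- The coaching and diary descriptions give no load rule.

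Nothing shown reverses or clarifies the sentence.

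**The case against.** The strongest reply is that this is loose English and not a design decision. The sentence is introduced as encouraging progression, so the authors surely meant a participant who outperforms the prescription. That is probably right. It does not repair the text, because two different rules fit that intention (Alternatives A and B above) and a reader cannot tell which one was used.

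A second reply is that the operative instruction lies outside the article: in the website, Fig. 5, the supplementary prescription tables and the cited source trial. The prototype also went through a usability and safety test in 11 patients (Intervention development). This limits the finding to the printed sentence and rules out any claim that participants were misdirected. It is not a matter of detail left to a supplement, though, since the article states the rule and states it in the wrong direction.

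A third reply is that safeguards remain:

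- the eligibility exclusions
- autoregulation through fatigue, pain and confidence ratings
- the safety module on when to stop exercising
- the diary's exertion and pain records
- the week-three compliance check
- the coaching calls and weekly remote review

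All of these stand, and they lower the likely consequence for a participant. None of them makes the printed trigger correct, and someone working from the article alone would still copy it.

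**Conclusion.** The concern holds for the sentence as printed. It ties a 5-10% load increase to effort above the prescribed OMNI level, which is the reverse of a rule that keeps effort at 7-8. For a target of 7, a target of 8 or the whole band, no rating that triggers the printed rule would trigger either plausible intended rule.

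This rests on the ordinary meaning of exceeding an exertion standard, on the scale direction implied by the article's own labels, and on whole-number ratings for the counts. Slip or not, it is a dosing instruction in the Methods and should be corrected. No harm estimate is made, and sample size, analysis and success criteria do not change.

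**What to change.** Replace the trigger with one of two wordings, according to what the sponsor intended:

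- *Increase resistance by 5-10% if perceived exertion was below the prescribed level in each set completed.*
- *Increase resistance by 5-10% if the prescribed repetitions were exceeded at or below the prescribed exertion in each set completed.*

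Then read through the website exercise plan, the diary, the coaching wording and the "written exercise instructions to aid both safety and efficacy" to confirm that they state the rule in the same direction.

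The cost is one protocol sentence and that read-through. If participant-facing text has to change, it goes through the steering committee and ethics route in Protocol changes. No extra staff, visits or participants are needed.

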**Fig. 5 Fig5:**
[figure not shown]
Modified illustrations of the OMNI exercise scale of perceived exertion, (**a**) resistance training, (**b**) aerobic training

**Table 3 Tab3:** Resistance training prescription

Exercise type	Volume of exercise prescribed (sets x repetitions)			
	Week 1	Week 2	Week 3	Weeks 4-8
Upper body exercises	2 × 12	2 × 12	3 × 12	2-3 × 12-8 (see Additional file 3 for specific prescription)
Trunk exercises	2 × 8	2 × 8	2 × 10	2-3 × 10-12 (see Additional file 3 for specific prescription)
Lower body exercise	2 × 12	2 × 12	3 × 12	2-3 × 12-8 (see Additional file 3 for specific prescription)

Frequency of resistance training will be 2 days per week for the first 3 weeks and then increased to three sessions if the participant was able to adhere. Participants already completing one or more sessions per week prior to the intervention starting will be required to complete at least two sessions per week of the Exercise Guide programme and will be encouraged to complete more sessions of their own prescription if they wish.

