**Fig. 2 Fig2:**
[figure not shown]
Study flow diagram

To be eligible, participants must have been diagnosed with metastatic prostate cancer (as confirmed by their physician) and have medical clearance from their physician (General Practitioner, Medical Oncologist, Radiation Oncologist or Urologist). Physicians are required to provide details regarding the extent and location of metastases. Participants also need to have access to a computer with the internet, be able to read and write in English and provide written consent prior to baseline testing. Finally, to be eligible participants should not already engage in two sessions of resistance-training and 60 minutes of structured moderate-vigorous aerobic exercise per week. Participants meeting one target but not the other will be eligible.

Patients will be deemed ineligible if they have any absolute contraindications to performing moderate physical activity (resistance, aerobic and flexibility) for at least 20 min (in bouts of 5 min), up to 2 days of the week. This includes no recent serious cardiovascular events (within 12 months), unstable bone metastases, spinal compressions or acute illness and infection [36]. Participants will also be excluded from the study if they have moderate to severe bone pain (Common Terminology Criteria for Adverse Events V.5.0 grading criteria).

Participant retention strategies will include flexible scheduling for telehealth consultations, reminder calls/texts and consistent study staff. Criteria for discontinuing intervention include participant request and worsening conditions which are absolute contraindications to exercise (including unstable bone metastasis, spinal compression and significant cardiovascular events). Concomitant care will be permitted during the study and any changes in treatment will be recorded.

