### Exercise guide intervention

#### Intervention development

Development of the intervention (ExerciseGuide) was guided by the Intervention Mapping protocol [37], which involves a needs assessment, identification of determinants of the desired intervention outcomes and the selection of theory-based and evidence-informed strategies to target key determinants or change objectives. The process was undertaken predominantly by HE and CES, in collaboration with consumer representatives, hence drawing on expertise in exercise prescription, behaviour change and the lived experience of prostate cancer. An overview of the development process, including original research conducted and theories considered is described below.

In brief, a qualitative interview study (*N* = 18) was completed to better understand the needs and preferences of individuals in this population. This was conducted alongside a systematic review of online interventions for prostate cancer patients to determine feasibility, acceptability and efficacy, as well as factors associated with success (or failure) [38]. These studies highlighted that online supportive care interventions are acceptable in individuals with prostate cancer. Participants within the qualitative study stressed the importance of individualised exercise prescription, the need for evidence-based educational content, support and feedback to aid adherence. Importantly, participant’s accuracy of reporting metastasis location and extent was mixed, indicating further reporting measures would be required to ensure appropriate prescription.

The selection of theory to guide intervention development was informed by our original research, and evidence in the fields of exercise and health psychology more broadly [39–44]. A summary of the theories used and associated implications is provided in Supplementary Table 1. Of note, a variety of theories were considered necessary to draw upon based on the premise that exercise behaviour is guided by dual processes, and that for longer-term behaviour change to occur; it is necessary not only to address social-cognitive determinants like self-efficacy but also to address how people feel and the extent to which their behaviour change process is habit-forming in nature [41, 43]. Theory was also used to inform the architecture of the intervention and the provision of computer-tailored feedback (self-determination theory and elaboration likelihood model) [45, 46].

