**Fig. 3 Fig3:**
[figure not shown]
Screenshot of the Exercise Guide home page and one page of the My Exercise Plan module

Modules include evidence-based information on the safety and benefits of physical activity, an individually tailored exercise programme, behaviour change information, self-monitoring, lifestyle information and other resources of use (Table 1). Based on the previous qualitative work in this area, participants will receive access to all modules as soon as they complete the initial introduction module and are free to complete the modules in order of personal priority.

**Table 1 Tab1:** Overview of tailored modules included in 8-week intervention (page 10)

Module title	Module goal(s)	Tailoring variable	Mechanisms of action
**Getting started** (how to use this site)	Introduce the programme, including how to navigate the site.	Nil.	• Self-efficacy
**My exercise Plan** (week 1-3)	Provide individualised exercise prescription to participants.	The aerobic training component of the study is based on metastases location, current aerobic modes, current duration and frequency completed and pain levels. Self-reported ability which includes current fatigue levels, experience and confidence, will also be taken into account (14). Resistance exercise prescription is be tailored to the individual based on metastasis location pain or injury location, current fatigue levels and both resistance training experience and confidence. Favoured modes of exercise and access to equipment is taken into account for both aerobic and resistance training.	• Self-efficacy • Intentions
**My exercise plan** (week 4-8)	Progression of exercise prescription on current exercise levels.	Current aerobic exercise levels (current duration and frequency completed). Current resistance training levels (session frequency and percentage of sets and reps completed) Repeated questions from My Exercise Plan (week 1-3) with previous answers. Participants asked to re-evaluate their answers and change if needed.	• Self-efficacy • Intentions

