**Exercise benefits** (what does exercise actually do?)	Help men to develop a deeper understanding of the benefits of exercise, and how these benefits accrue. Highlight benefits that are personally relevant. Strengthen intentions to participate in structured exercise.	Health issues that may be improved through exercise (e.g. fatigue, poor sleep, muscle weakness) Exercise types currently participated in (aerobic and resistance).	• Outcome expectations and identified regulation of motivation. • Proximal intentions (goals)
**Drive safely** (how to exercise safely)	Provide men with tailored information regarding safety implications to promote educational empowerment. Provide an understanding of when exercise should be terminated to avoid risk of injury.	Cancer-specific considerations that may impact the safety of exercise prescription; specifically, current treatment/disease side effects (e.g., fatigue, neuropathy) and treatments (e.g., chemotherapy, androgen deprivation therapy). Co-morbidities (e.g., diabetes, osteoarthritis) were also taken into account [10, 49].	• Self-efficacy • Outcome expectations/knowledge
**How are you tracking?** (map your progress each week)	Facilitate self-monitoring of exercise behaviours and exercise outcomes, with the aim of strengthening self-regulation.	Date, frequency of exercise, satisfaction with goal, motivation, planning score, habit scores, perceived fitness and overall fatigue, mood and pain.	• Self-efficacy • Self-regulation • Intentions
**Making it last** (strategies for building lasting exercise habits)	Support the adoption and maintenance of health-enhancing exercise behaviours.	Structured exercise programme status (interested but not commenced, commenced but finding it hard to adhere to, commenced and finding it easy to adhere to), barrier self-efficacy, exercise planning behaviours, automaticity of exercise.	Adoption • Self-efficacy • Self-regulation • Intentions Maintenance • Intrinsic motivation • Enjoyment • Automaticity (habits)
**Exercise +** (what else can you do to keep healthy?)	Increase health literacy regarding other lifestyle factors that may impact on health and quality of life besides structured exercise. Provide links to further information. Provide men exhibiting high distress with information on where to find help.	Current diet, sitting time, alcohol consumption, sleep quality, hot flushes, distress.	• Increasing knowledge • Sign-posting • Competence

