##### Muscular strength

The one-repetition maximum method will be utilised to determine muscular strength [14]. The leg extension will be used to determine lower limb strength, and the chest press will assess upper limb strength. Patients with proximal femur bone lesions will be excluded from the leg extension one-repetition maximum test, whereas those with rib, thoracic spine lesions and or humerus lesions will be excluded from the chest press one-repetition maximum test.

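### Extra self-prescribed resistance sessions are encouraged without the lesion-site limits that the plan applies to its own sessions and strength tests

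*Protocol article*

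**What the plan says.** The Resistance-based component section addresses men who did one or more resistance sessions a week before entry. They must do at least two weekly sessions from ExerciseGuide and "will be encouraged to complete more sessions of their own prescription if they wish". No condition on lesion site is attached.

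Elsewhere the plan uses lesion site as a limit:

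- Table 1, My exercise Plan: "Resistance exercise prescription is be tailored to the individual based on metastasis location pain or injury location".
- Web-based exercise prescription, Table 2, headed "Modified multimodal exercise prescription for individuals with bone metastases": upper-body resistance is left blank for proximal humerus lesions and lower-body resistance for proximal femur lesions. Footnotes bar shoulder movements for cervical and thoracic/rib lesions, and hip flexion and extension for pelvic lesions.
- Muscular strength: "Patients with proximal femur bone lesions will be excluded from the leg extension one-repetition maximum test". Rib, thoracic spine and humerus lesions rule out the chest press test.

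Lesion locations come from the treating doctor. Participants and screening says: "Physicians are required to provide details regarding the extent and location of metastases".

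**The concern.** The sentence separates two kinds of session: those belonging to ExerciseGuide, and those of the man's own prescription. The first kind is shaped by lesion site. The second is actively encouraged and has no stated limit on region or movement.

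What is at stake is participant safety. The plan treats certain loading as unsuitable for men with lesions at certain sites, even after clearance and with unstable disease excluded. A man who follows the printed encouragement could do that same loading in a session that the trial invited him to add.

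**Working it through.** There is no figure to reproduce and no arithmetic applies. The check compares what the document says about each kind of loading, then asks whether any described safeguard covers the gap.

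**1. Can the affected group exist?** Yes. Participants and screening bars only men who meet both the resistance and the aerobic target, so a man who already does two resistance sessions a week can enrol if his aerobic exercise is below target. Men with stable bone lesions can also enrol. The Introduction puts bone metastases at over 80% in advanced prostate cancer, which is background and not trial data.

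**2. Which loading carries a site limit?**

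| Loading | Lesion-site limit stated? | Where |
|---|---|---|
| ExerciseGuide resistance sessions | Yes | Tables 1 and 2 |
| One-repetition maximum tests | Yes | Muscular strength |
| Prescribed exercises repeated on own equipment | Inherits the programme's limits | Resistance-based component |
| Extra sessions of own prescription | No | Resistance-based component |

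**3. Does a described safeguard supply the limit?**

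| Safeguard | What it does | Site limit for own sessions? |
|---|---|---|
| Clearance and exclusions (Participants and screening) | Removes unstable metastases, spinal compression and moderate to severe bone pain | No; stable lesions remain |
| Drive safely module (Table 1) | Tailored on "specifically, current treatment/disease side effects (e.g., fatigue, neuropathy) and treatments (e.g., chemotherapy, androgen deprivation therapy" and on co-morbidities; also teaches when to stop | None described |
| Autoregulation (Web-based exercise prescription) | Changes the website prescription when questions are re-answered | No |
| Coaching (Tele-health coaching and monitoring of progress) | Calls in weeks one and three, weekly review and feedback | None described |
| Diary (Additional components) | Records exercises and pain | No; it records and does not restrict |

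**4. Worked case.** Take a man with a stable proximal femur lesion who did one weekly resistance session before entry. Table 2 gives him no lower-body resistance work, and he is barred from the leg extension strength test. The same plan encourages him to add sessions of his own with nothing said about the lower body.

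**5. A caution on Table 2.** The programme also draws on an "isometric spinal exercise prescription", so the blank trunk cells for spinal lesions may not be the limits actually applied. Any condition should therefore refer to Table 2 as applied in the man's own plan, not to Table 2 alone.

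**The case against.** The strongest reply is that this is a condensed article. Safety instructions of this kind would normally sit in the website modules, coaching content, supplementary files and participant materials, none of which is shown, and they may already restrict these sessions. The listed tailoring variables of Drive safely are also not the whole module. That stands as a limit on the claim, which concerns only the text at hand. It does not remove the point, because the article prints a positive encouragement and leaves off a condition that it applies to comparable loading.

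A second reply is that own prescription may mean an established routine, perhaps set by a professional, in men with medical clearance. That is possible, and some of these sessions would then add no exposure beyond pre-entry training. Reading the phrase as the man's tailored ExerciseGuide plan is less plausible, since the sentence contrasts it with ExerciseGuide sessions.

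Two stronger readings are tempting and are not supported:

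- A reader might infer that trial participants will not know which regions to avoid, because Intervention development reports that "accuracy of reporting metastasis location and extent was mixed, indicating further reporting measures would be required to ensure appropriate prescription". That finding comes from an earlier interview study (N = 18). It does not show what men know after receiving a tailored plan and speaking with an exercise physiologist.
- A reader might count the blank or restricted cells of Table 2 as a measure of risk. Such a count says nothing about how many men, sessions or injuries are involved.

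**Conclusion.** The point holds as a minor safety clarification, to be considered by the sponsor. Extra resistance sessions of the participant's own prescription are encouraged without the lesion-site limits that govern the programme's own sessions and its strength tests, and no safeguard described in the article states such a limit for them.

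Its size cannot be given. The document does not say how many participants train already, how many of those have bone lesions, or how many extra sessions they would do. The sessions are optional and partly pre-existing, so the added risk may be small or nil. Sample size and analysis are unaffected.

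The conclusion assumes that own prescription means sessions outside ExerciseGuide, and that no unshown trial material already imposes the limit. If such material does, only the article's sentence needs aligning with it.

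**What to change.** Keep the encouragement and add one condition to the sentence in Resistance-based component: *provided that participants with bone metastases avoid the regions and movements excluded for their lesion sites (Table 2, as applied in their ExerciseGuide plan)*.

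At the week-one call already scheduled, the exercise physiologist tells each such participant which regions and movements these are, using the metastasis locations supplied by the physician. This does not rely on the website displaying exclusions, which the article does not say it does, and it needs no new data.

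Cost: one clause and one item in an existing call. Recruitment has begun, and the Protocol changes section requires Steering Committee approval and ethics resubmission for amendments, so the change is best bundled with any other. Some men may drop exercises they did before entry, so their training volume may fall slightly.
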